## Methods/design

The present study is a prospective, confirmatory, cluster-randomised, multi-centre, international phase III trial with two parallel groups (intervention vs. TAU) and three trial phases (baseline assessment, 12 weeks of treatment, 12 [±1] weeks of follow-up observation). The intervention condition is incorporated into the usual standard care within residential care (START NOW + TAU) vs. TAU. A randomised controlled AB-BA design will be used. Institutions will be randomised to start either with the intervention group (A) or with the control group (B) (TAU). After having conducted A or B, each institution will run the other condition: Institutions starting with TAU receive START NOW, and institutions that finished START NOW and the follow-up assessment conduct a new group with TAU, whereby strict rules are defined to eliminate the risk of carry-over effects.

### Study centres

The study will take place at youth welfare institutions located in proximity to four clinical trial centres. Study centres include the departments of child and adolescent psychiatry at the university hospitals in Basel, Switzerland (CS, principal investigator); Frankfurt, Germany (CMF); Aachen, Germany (BHD); and Amsterdam, The Netherlands (AP). Data management as well as biometric and statistical support are provided by the Institute of Medical Biometry and Informatics (IMBI), University of Heidelberg, Germany. The Coordination Centre for Clinical Trials (Koordinierungszentrum für Klinische Studien [KKS]) at the University of Heidelberg is in charge of study monitoring.

### Participants

Several youth welfare institutions will be asked to participate. If they agree, female adolescents in the institutions who are aged 12–20 years and their legal guardians will be asked if they want to participate. Diagnostic assessment will be standardised according to criteria of the *Diagnostic and Statistical Manual of Mental Disorders, Fourth Edition, Text Revision* (DSM-IV-TR) or the *Diagnostic and Statistical Manual of Mental Disorders, Fifth Edition* (DSM-5). Diagnostic information is obtained via a semi-structured clinical interview (K-SADS-PL). Inclusion and exclusion criteria are listed in Table 1.

**Table 1 Tab1:** Inclusion and exclusion criteria

Inclusion criteria	Female adolescents aged 12–20 years
	Diagnosis of current CD (DSM code 312.8) and/or ODD (DSM code 313.81)
	Sufficient writing and reading skills (in German or Dutch)
Exclusion criteria	History or current clinical diagnosis of autism spectrum disorder according to ICD-10, DSM-IV-TR or DSM-5 (autism, Asperger syndrome, pervasive developmental disorder-not otherwise specified, atypical autism, autism spectrum disorder)
	History of or current clinical diagnosis of schizophrenia according to ICD-10, DSM-IV-TR or DSM-5
	Current clinical diagnosis of bipolar disorder or mania according to ICD-10, DSM-IV-TR or DSM-5 (History of bipolar disorder or mania is not an exclusion criterion for individuals with CD.)
	Fetal alcohol syndrome according to ICD-10, DSM-IV-TR or DSM-5
	Known monogenetic disorder, genetic syndrome (e.g., fragile X syndrome, Down syndrome, Prader-Willi syndrome)
	Any chronic or acute neurological disorder (e.g., cerebral palsy, motor problems due to motor or metabolic disorder, current treatment for epilepsy, history of severe traumatic brain injury) (Mild traumatic head injury without loss of consciousness is not an exclusion criterion.)
	Any valid indication of IQ <70 (e.g., special education, previous test results)
	Severe medical condition interfering with the intervention, including suicidal ideation
	Concurrent group-based psychotherapeutic treatment such as START NOW, DBT-A or similar interventions

*Abbreviations: CD* Conduct disorder, *DBT-A* Dialectical behaviour therapy for adolescents, *DSM-IV-TR Diagnostic and Statistical Manual of Mental Disorders, Fourth Edition, Text Revision*, *DSM-5 Diagnostic and Statistical Manual of Mental Disorders, Fifth Edition*, *ICD-10* International Classification of Diseases, Tenth Revision, *IQ* Intelligence quotient, *ODD* Oppositional defiant disorder

### Criteria for withdrawal

Participants may withdraw from the study (1) at their own request or the request of their parents/legal representatives; (2) if, according to the investigator’s opinion, participation in the trial would be harmful for the participant’s well-being; or (3) if the participant’s behaviour significantly disturbs and impedes group sessions due to, for example, aggressive behaviour directed toward other group members or herself.

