### The present study

Within the framework of the FP7 project Neurobiology and Treatment of Adolescent Female Conduct Disorder: The Central Role of Emotion Processing (FemNAT-CD; see http://www.femnat-cd.eu/ for more information), a European multi-disciplinary study, the aim of the present study is to evaluate the effects of an adapted, gender-specific START NOW intervention for females with ODD/CD living in youth welfare institutions. To our knowledge, no prior study has evaluated the effects of such a CBT-based intervention combining aspects of multiple other therapeutic approaches for this specific population in the youth welfare sector. The adaptation of the original START NOW intervention still employs the same underlying principal components of the skills training, but it uses a slightly modified framework (i.e., individual sessions on top of group sessions to enhance personal understanding and relevance of content; shortened length of the programme due to frequent temporary, time-constrained placements) and adjusted content (i.e., illustrations and theme stories tailored to teenage girls’ interests). Furthermore, the intervention will be conducted by staff members of the respective youth welfare institution. Intensive pre-training and supervision, including fidelity monitoring, will be provided. The intervention comprises weekly group sessions (14 sessions, 90 minutes each) and individual sessions (45 minutes each). The aim of the individual sessions is to ensure the transfer of the content of the group training into the personal, daily routines of the participants. Girls are encouraged to practice the skills introduced during the START NOW training between sessions in their daily social interactions with the aid of the responsible social worker. In addition, parents will be sent information on START NOW and information regarding efficient parenting strategies and communication skills with adolescents. In essence, key aspects of the START NOW skills training have remained the same within the adapted version and are well-suited for the target population that can, similarly to the target population of the original format, be described by emotional regulation deficits, many invalidating and traumatic relationship experiences, high impulsivity and a low motivation for change.

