### Concomitant treatment

Additional treatments administered to the participants on entry into the trial or at any time during the study are documented as concomitant treatments on the respective pages of the case report form (CRF). Concomitant treatments are allowed in the intervention group as well as the control group as long as they do not represent a group-based psychotherapeutic approach. Examples of concomitant treatments include individual psychotherapy or external support activities that serve to strengthen social-emotional, cognitive or physical competencies (e.g., drama club, chess club, soccer). Medication and changes in dosage will also be documented throughout the study.

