### Measurement time points

Assessments will be conducted at baseline (T1), 6 weeks after the start of the intervention (mid-treatment [T2]), 3 months after the start of the intervention (end of treatment [T3]) and 3 months after the end of the intervention (T4). The flow of participants from recruitment through the end of the study is shown in Fig. 1. To promote participant retention, regular contact with participants through telephone calls, on-site visits and information letters is provided. Furthermore, participants who discontinue the intervention but are still interested in taking part in the data assessments are nevertheless assessed. Because the number of sessions attended is a control variable in the analysis, continuing data collection with participants who are drop-outs is not a problem.

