### Primary outcome measure

The primary outcome variable is defined as change in number of fulfilled CD/ODD diagnostic criteria as assessed by a standardised, semi-structured clinical interview between baseline and post-treatment and between baseline and follow-up. The K-SADS-PL will be used [72, 73]. Interviewers will be trained by an experienced clinician, and regular consensus meetings will be held. The K-SADS-PL is a widely used and validated semi-structured diagnostic interview designed to assess current and past episodes of psychopathology in children and adolescents according to DSM-IV-TR/DSM-5 criteria. Interviews are conducted with the adolescent as well as with a social worker from the participant’s respective youth welfare institution who is not involved in the intervention. Symptom measures, diagnoses and severity ratings derived from the interview are based on the obtained information combined with clinical judgement. Thus, summary ratings are achieved by including all sources of information.

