### Statistical methods

The full analysis of the primary outcome measure will be conducted on the basis of the intention-to-treat (full analysis set) population, including all randomised patients. To account for the data structure, a linear mixed model with the primary endpoint (change in ODD/CD score between baseline and end of intervention) as the response variable, including baseline CD/ODD symptoms, group, age, site and IQ as fixed factors and the respective cluster as a random factor, will be applied. The random intercept, as well as the residuals, will be assumed to be normally distributed. The correlation structure can be referred to as compound symmetry [102], which is a common assumption in cluster-randomised trials [103]. The results will be presented as the mean between-group difference with the corresponding two-sided 95% confidence interval. The associated Hedges’ effect size *g* [104] will be calculated, in addition to the practice-related intra-cluster correlation coefficient. To fit the primary model, the restricted maximum likelihood approach will be used.

The overall type I error rate is set at α = 5% (two-sided) and will be controlled by applying the multiple test procedure for hierarchically ordered hypotheses. The first null hypothesis states that the change in ODD/CD score between baseline and end of intervention is equal for both the intervention and control groups (H_0I_: μ_1I_ = μ_2I_). This hypothesis will be tested at a two-sided level of significance of 5% against the alternative hypothesis (H_1I_: μ_1I_ ≠ μ_2I_). Only if the first hypothesis can be rejected will the second null hypothesis, which states that the change between baseline and follow-up (12 weeks after end of intervention) will be equal in both groups (H_0II_: μ_1II_ = μ_2II_), be tested in the same way. This second hypothesis can then be tested also at a two-sided level of significance of 5% against the alternative hypothesis (H_0II_: μ_1II_ ≠ μ_2II_). Application of this multiple test procedure for hierarchically ordered hypotheses assures control of the overall type I error rate of 5%. Both null hypotheses will be tested by applying a random effects model that includes baseline CD/ODD symptoms, group, age, institution and IQ as fixed factors and cluster as a random factor. This statistical analysis plan was specified before the opening of the database.

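### Withdrawal criterion (3) applies only to START NOW and is worded as leaving the study; reconcile it with the promise to keep assessing girls who stop the intervention.

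*Protocol article*

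**What the plan says.** The list under Criteria for withdrawal (protocol article) opens: "Participants may withdraw from the study (1) at their own request or the request of their parents/legal representatives". Ground (2) is the investigator's opinion that "participation in the trial would be harmful for the participant’s well-being". Ground (3) is that the participant's "behaviour significantly disturbs and impedes group sessions due to, for example, aggressive behaviour directed toward other group members or herself". All three hang on the same opening words, so ground (3) is written as leaving the study, not as leaving the sessions.

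Measurement time points says that "participants who discontinue the intervention but are still interested in taking part in the data assessments are nevertheless assessed".

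The other relevant statements are:
- **Group sessions.** The section The present study makes 14 weekly group sessions part of START NOW. Table 1 excludes girls in concurrent group psychotherapy, and Concomitant treatment adds: "Concomitant treatments are allowed in the intervention group as well as the control group as long as they do not represent a group-based psychotherapeutic approach".
- **Outcome.** Primary outcome measure defines it as "change in number of fulfilled CD/ODD diagnostic criteria as assessed by a standardised, semi-structured clinical interview", from baseline to post-treatment and from baseline to follow-up.
- **Analysis.** Statistical methods uses the "intention-to-treat (full analysis set) population, including all randomised patients", with baseline CD/ODD symptoms in the model. The sample size section announces imputation as a partial remedy for missing values and allows 15% drop-out, not split by arm or reason.

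**The concern.** A girl in the control condition has no trial group session to disrupt, so ground (3) cannot apply to her. In START NOW it can, and the example given for it is aggression, which is close to what the primary outcome counts. A girl removed on this ground may well be one whose symptoms have not improved.

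If leaving the study means that no interview is held at T3 or T4, START NOW loses outcomes through a route that the control arm lacks and that may be related to the outcome. The remaining START NOW girls would then look better than the arm as randomised. Both confirmatory hypotheses are exposed, because one uses T3 and the other T4. A second risk is inconsistency: with two provisions that can be read differently, sites may treat the same situation in different ways.

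**Working it through.** **Reading the two provisions together.** Criteria for withdrawal speaks of leaving the study. Measurement time points speaks of discontinuing the intervention, and makes later assessment depend on the girl's interest. A girl who meets ground (3) could fall under either, and the article does not say which.

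**The plan's own figure.** Inputs from the sample size section: expected changes 3 and 1 (difference 2), SD 3.5, two-sided α 5%, power 80%, design effect 1.08, drop-out 15%.
- The exact two-sample t test gives 50 per arm; 2 × 50 × 1.08 = 108, as stated.
- 108 / 0.85 = 127.1, rounded up to 128, as stated; an equal split is 64 per arm.

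The sample size reproduces and is not affected by this point. The 15% allowance protects power, not balance between the arms.

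**Possible bias.** Two inputs are assumptions, not in the documents: f, the share of START NOW girls removed under ground (3) without later interviews, and r, the correlation between the tendency to be removed and poor change. If removal takes the upper tail of a normal trait, the START NOW mean among observed girls is too favourable by

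b = 3.5 × r × φ(z) / (1 − f), with z the (1 − f) normal quantile.

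- f = 5%: φ(z)/(1 − f) = 0.1031 / 0.95 = 0.109, so b = 0.38 × r.
- f = 10%: 0.1755 / 0.90 = 0.195, so b = 0.68 × r.

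For the type I error of a single test with no true effect and no loss in the control arm: SE = 3.5 × √(1.08 × (1/(64(1 − f)) + 1/64)), and the rejection probability is 1 − Φ(1.96 − b/SE) + Φ(−1.96 − b/SE). SE is 0.65 at f = 5% and 0.66 at f = 10%.

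| f (girls of 64) | r | b (symptoms) | b as share of planned 2 | type I error |
|---|---|---|---|---|
| 5% (about 3) | 0.2 | 0.08 | 4% | 5.2% |
| 5% | 0.5 | 0.19 | 10% | 6.0% |
| 5% | 1.0 (ceiling) | 0.38 | 19% | 9.0% |
| 10% (about 6) | 0.2 | 0.14 | 7% | 5.5% |
| 10% | 0.5 | 0.34 | 17% | 8.1% |
| 10% | 1.0 (ceiling) | 0.68 | 34% | 17.8% |

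This is an unadjusted observed-case calculation. The planned model adjusts for baseline symptoms and uses an imputation method that the article does not name, so the table illustrates the scale and does not predict the trial's result. If the girls are assessed at T3 and T4, b is zero.

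**The case against.** The strongest defence is that the article already intends to follow girls who drop out. The withdrawal wording is permissive (participants may withdraw), Measurement time points offers continued assessment, and calls, visits and letters are planned to keep girls in the trial. This stands in large part. A reader might infer that the protocol removes the most aggressive girls and never collects their outcomes; the documents do not support that. They leave the matter open, which is a lesser fault. The defence is incomplete because the offer covers stopping the intervention, not leaving the study, and depends on continuing interest. The article also reasons that following drop-outs is unproblematic because session attendance is controlled for, yet neither model description in Statistical methods contains that variable.

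Second, disruptive girls need not be poor responders. The outcome is a change, the model adjusts for baseline, aggression is only an example of disruption and includes self-directed aggression, and the symptom count covers non-aggressive criteria too. This stands: the link to the outcome is plausible but not shown, which is why r starts at 0.2 and why r = 1.0 is only a ceiling.

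Third, a reader might infer that outcome-related loss occurs in one arm only. That does not hold either. Grounds (1) and (2) apply to both arms and may also be related to outcome; only ground (3) is one-sided.

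Fourth, the imputation method may properly be left to a statistical analysis plan. That is accepted, and its absence here is no finding. But the article itself calls imputation a partial remedy, and any method that models removed girls on those who stayed would be too favourable if removal follows worsening.

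**Conclusion.** The point holds as an unresolved conflict between two provisions, with a possible bias attached. Ground (3) opens a route to missing T3 and T4 interviews that exists only in START NOW, may be related to the outcome, and could favour START NOW. An intention-to-treat set cannot restore interviews that were not held.

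The size cannot be derived from the documents. With 5–10% removed and r between 0.2 and 0.5, the bias is about 0.1–0.3 symptoms, or 4–17% of the planned difference of 2, with a type I error of 5.2–8.1%. The figure of 0.7 symptoms (34%) requires both 10% removal and session disruption that identifies the worst change scores perfectly; it should not be quoted as the expected effect. All of these figures assume that no later interviews are held and that only observed cases are analysed.

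**What to change.** Reconcile Criteria for withdrawal with Measurement time points by adding one statement. Whatever is decided clinically about attending sessions, meeting ground (3) does not by itself end study participation. Subject to consent and to ground (2), the T3 and T4 K-SADS-PL interviews with the girl and the social worker are still sought, and the girl is analysed in the condition to which she was randomised. Leave grounds (1) and (2) as they are; restricting study withdrawal to withdrawn consent would delete the welfare ground (2), and the fix does not need that. No position is taken here on when a girl should leave the group.

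Report the number of ground (3) cases and how many were assessed at T3 and T4. Add a sensitivity analysis that imputes unassessed cases unfavourably, for example with no change from baseline. This is deliberately harsh, since the plan expects an improvement of 1 even under usual treatment. Compared with giving these girls the planned START NOW change of 3, it lowers the START NOW mean by 0.05 × 3 = 0.15 to 0.10 × 3 = 0.30 symptoms if 5–10% are affected.

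The cost is a sentence in the protocol, submitted as the formal amendment that the article requires for any modification, one line in the participant flow report and one extra analysis. The visits are already scheduled. The change is best made while they are still to come, because interviews not held on time cannot be recovered later.

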### Concomitant treatment

Additional treatments administered to the participants on entry into the trial or at any time during the study are documented as concomitant treatments on the respective pages of the case report form (CRF). Concomitant treatments are allowed in the intervention group as well as the control group as long as they do not represent a group-based psychotherapeutic approach. Examples of concomitant treatments include individual psychotherapy or external support activities that serve to strengthen social-emotional, cognitive or physical competencies (e.g., drama club, chess club, soccer). Medication and changes in dosage will also be documented throughout the study.

### Measurement time points

Assessments will be conducted at baseline (T1), 6 weeks after the start of the intervention (mid-treatment [T2]), 3 months after the start of the intervention (end of treatment [T3]) and 3 months after the end of the intervention (T4). The flow of participants from recruitment through the end of the study is shown in Fig. 1. To promote participant retention, regular contact with participants through telephone calls, on-site visits and information letters is provided. Furthermore, participants who discontinue the intervention but are still interested in taking part in the data assessments are nevertheless assessed. Because the number of sessions attended is a control variable in the analysis, continuing data collection with participants who are drop-outs is not a problem.

**Fig. 1 Fig1:**
[figure not shown]
Trial flowchart. *TAU* Treatment as usual

### Primary outcome measure

The primary outcome variable is defined as change in number of fulfilled CD/ODD diagnostic criteria as assessed by a standardised, semi-structured clinical interview between baseline and post-treatment and between baseline and follow-up. The K-SADS-PL will be used [72, 73]. Interviewers will be trained by an experienced clinician, and regular consensus meetings will be held. The K-SADS-PL is a widely used and validated semi-structured diagnostic interview designed to assess current and past episodes of psychopathology in children and adolescents according to DSM-IV-TR/DSM-5 criteria. Interviews are conducted with the adolescent as well as with a social worker from the participant’s respective youth welfare institution who is not involved in the intervention. Symptom measures, diagnoses and severity ratings derived from the interview are based on the obtained information combined with clinical judgement. Thus, summary ratings are achieved by including all sources of information.

### Secondary outcome variables

Further objectives of the present trial are to assess pre-post changes in different aggression phenotypes and CD/ODD-related outcome measures in girls participating in the START NOW training compared with those receiving TAU. In adolescents, the Reactive-Proactive Aggression Questionnaire [74], used to distinguish between reactive and proactive/instrumental forms of aggression, and the Relational Aggression Questionnaire [75], which assesses relational aggression strategies such as excluding members of the peer group or spreading gossip, will be used. The Child Behaviour Checklist [76] is used to assess various externalising (attention problems, aggression, delinquency) and internalising (e.g., anxiety/depression) symptoms in adolescents via self- and parent-report. The Affective Reactivity Index (as self-rating form and as caretaker rating) [77] is used to capture general irritability. To assess psychopathic traits, the Youth Psychopathic Traits Inventory [78] will be used. Next to this self-rating questionnaire, the Inventory of Callous-Unemotional Traits, Parent Report [79], will be obtained from parents to capture change in parent-reported callous-unemotional traits. Social workers will rate aggression symptoms in daily-life situations with the modified Overt Aggression Scale originally developed by Yudolfsky et al. [80]. In adolescents also, a time-sampling short assessment procedure (ecological momentary assessment) will be used with measures collected twice daily (after lunch and after supper on 4 consecutive days; pre-, mid- and post-assessment) to capture current emotions and regulation capacities while minimising retrospection effects and interference with the daily routine. To assess change in deliberate emotional regulation strategies, the Difficulties in Emotion Regulation Scale [81] will be used.

Each female adolescent will define individual goals, and their attainment will be investigated on the basis of Goal Attainment Scaling [82]. In addition, general life satisfaction of the adolescents [83] will be assessed with the Brief Multidimensional Students’ Life Satisfaction Scale. Caretakers’ self-efficacy, burn-out symptoms and job satisfaction will be assessed with the Burnout Screening Scale, a composite instrument comprising different questionnaires [84–88]. In the intervention group, the clients’ and trainers’ satisfaction with the programme will be assessed (Client Satisfaction Questionnaire/Training Satisfaction Questionnaire) [19].

